8.1 Primary Outcome

For Year One and Year Two, we will calculate the mean difference in immunization rates between the intervention year and baseline for both comparison groups. Assuming that the mean values are normally distributed within each group, we will use t-test to compare immunization rate difference means of the control group to the intervention group. We will consider *P* values < 0.05 to be significant.

Linear regression models will be used for continuous outcome variables (improvement in healthcare personnel immunization rates from the base year) and logistic models for binary outcome variables (attainment of the benchmark of 90% immunization rate set by the National Advisory Committee on Immunization). The assumptions for using each regression model will be checked and analyses adjusted accordingly. All analyses will be undertaken, adjusted for healthcare organization size, and for baseline variables which differ to a statistically significant extent between groups. Differential effects of the intervention by characteristics of healthcare organization and baseline rates will be assessed for the primary outcome measures by adding terms for the interaction between these characteristics and baseline rates and Intervention Group to the regression models.

Multilevel models will be applied to take account of clustering at the healthcare organization level and the Guide effects which will apply to differing extents in the intervention group (due to the effectiveness of campaigns in each participating healthcare organization). While the primary outcome will be attainment of the recommended benchmark of 90% set by the National Advisory Committee on Immunization, we will investigate the profile of immunization rate attainment at Baseline (2008-2009), Year One (2010-2011) and Year Two (2011-2012). This will be a repeated measures analysis. That is, evidence for differences in effect of the intervention at the different time points will be assessed.

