**Intervention Group – March 2011 and March 2012**

- Immunization rate data for each year
- Campaign Details Questionnaire
- Assessment of the Guide
- Assessment of the revised OIDA
- Assessment of the Toolkit

All questionnaires will be given as self-administered questionnaires and will be available online or via email. Each questionnaire will include check-box questions (which will be analyzed using descriptive analysis) and open-ended questions. The results from the open-ended questions and information gathered from the workshops, webinars, and teleconferences, plus interactions with the research team throughout the campaign season, will be summarized and synthesized in a post-campaign report each year.

1. **Study Outcomes**
   1. Primary Outcome

In the Intervention Group, a 10% improvement in healthcare personnel immunization rates from the base year (2008-2009) as compared to Year One (2010-2011) and Year Two (2011-2012)

This will be assessed by conducting a time-series analysis on how each organization does against themselves and between the Intervention and Control Group. In our systematic review of the effectiveness of influenza campaigns in healthcare organizations published in the Canadian Medical Association Journal (15) (see Appendix 2), methods for calculating change scores were used that enable comparisons across different types of studies randomized trials with only “after” assessments in the intervention and control groups as well as comparisons of studies that had change scores based on before and after the campaigns in control and intervention groups.

Also, we will assess the immunization rates against the benchmark of 90% set by the National Advisory Committee on Immunization (17).

- 1. Secondary Outcome

In both the Intervention and Control Group, we will assess improvement in the reporting of immunization rates, based on the methodology outlined in Appendix 3 of the Guide (16).

- 1. Tertiary Outcomes

Improvement in how each organization plans, implements, monitors, and evaluates their campaign will be observed. We will track this improvement comparing their campaign activities each year against the benchmarks established by the Checklist in the Guide.

Overall satisfaction with the Guide and with the delivery methods of the Guide, including preferences for web-based or paper tools, ease of use, practicality of application, and the need for outsider intervention, will be assessed.

1. **Sample Size**

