The sample size is based on both the number of healthcare organizations and the number of healthcare personnel in each organization. We aim to accumulate data on a minimum of 150 healthcare personnel per cluster over 2 years. Thus, if an organization is in the trial for two years they will have to contribute at least 300 healthcare personnel to the trial. Note that we define a cluster as a healthcare organization. Sample size was calculated based on the equations of Kelsey et al. for Randomized Clinical Trial Studies (18) and multiplied by the design effect to get the number of subjects required for the cluster design. The level of difference between intervention organizations and the control organizations set in determining the sample size was 20%. This requires randomization and evaluation of immunization campaigns in 46 healthcare organizations (clusters) with 6000 healthcare personnel. Twenty-three will be randomized to the intervention group. With an intra-cluster correlation coefficient set at 0.05 and an average cluster size of 150 eligible healthcare personnel per healthcare organization, we will need a total of 46 clusters for 80% power and 5% significance.

- 1. Statistical Methods

As outlined in the sample size calculation for the study, the statistical analysis will be based on analyses using cluster analytic techniques.

- 1. Interim Analysis and Stopping Rules

We will conduct an interim analysis after completion of Year One. There are no stopping rules.

1. **Randomization**
   1. Randomization Sequence Generation

After organizations have declared their willingness to participate in the study, they will be randomized to be in the Intervention Group or Control Group. Due to the relatively small number of healthcare organizations in the trial, minimization will be used to allocate participants to intervention and control to ensure maximum balance. After all participants have been recruited, organizations will be individually allocated to an intervention and/or control group by the Ottawa coordinating centre using computer-generated random number tables, embedded in a computer program for minimization. The variables to be used in the minimization process will be trial centre (Ontario and Manitoba) and healthcare organization size (small, medium, large).

Organizations assigned to the control group will be informed that they will have access to the Guide at the completion of the study.

- 1. Randomization Type

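### The primary comparison is tested at Year One and at Year Two, each at P<0.05, and no deciding year or success rule across the two years is stated

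*Protocol*

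**What the plan says.** The primary outcome under Study Outcomes is a 10% gain in staff immunization "from the base year (2008-2009) as compared to Year One (2010-2011) and Year Two (2011-2012"). Both seasons are named and neither is ranked.

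Section 8.1 turns this into tests: "For Year One and Year Two, we will calculate the mean difference in immunization rates between the intervention year and baseline" in each group, after which "we will use t-test to compare immunization rate difference means of the control group to the intervention group". One threshold applies to whatever is tested: P "values < 0.05 to be significant".

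The Sample Size section gives one error level for the trial: "we will need a total of 46 clusters for 80% power and 5% significance". The paragraph on interim analysis reads: "We will conduct an interim analysis after completion of Year One. There are no stopping rules".

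Two other statements in section 8.1 bear on the point. It calls reaching the national 90% target the primary outcome, whereas Study Outcomes defines the primary outcome as improvement from baseline and lists the 90% target as an additional assessment. It also plans a repeated-measures analysis to see whether the effect differs between time points.

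**The concern.** Two tests carry the primary label, and each is judged at 0.05 on its own. Nothing in the protocol links them: there is no deciding year, no requirement that both succeed and no division of the 5%. An investigator who follows section 8.1 literally can call the primary outcome significant in either year.

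Two things are at stake. First, the error rate for the main claim depends on a success rule that has not been written, and under one natural rule it exceeds 5%. Second, if one year is significant and the other is not, the protocol gives no way to say whether the Guide worked. The order of events makes this practical. Year One rates are collected in March 2011 and analysed at the interim, and Year Two rates follow in March 2012. A Year One result could be presented as the answer a year before the second test is possible.

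**Working it through.** **Inputs from the protocol.** 46 organizations, 23 to intervention and so 23 to control; 5% significance and 80% power; intra-cluster correlation 0.05; 150 personnel per cluster (Sample Size). Two change-from-baseline t-tests, each at 0.05 (section 8.1). Sidedness is not stated, so two-sided is assumed.

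**Reproducing the plan's own figure.** The design effect is 1 + (150 − 1) × 0.05 = 8.45. With 45% against 55%, the Kelsey formula gives (1.96 + 0.84)² × 2 × 0.5 × 0.5 / 0.10² = 392.4 per arm, using unrounded normal quantiles. Then 392.4 × 8.45 = 3316 people, and 3316 / 150 = 22.1, which rounds up to 23 clusters per arm, or 46 in all. So 46 fits one two-sided test at 5% for a 10-point difference near 50%. One-sided versions with a 10-point difference gave 32 to 38 clusters. A 20-point absolute difference gave only 8 to 14, so the 20% in the protocol cannot be an absolute difference on these inputs. That is a separate matter. What counts here is that the calculation provides for one test at one time point.

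**Correlation of the two tests (assumed).** Write B, Y1 and Y2 for an organization's rates in the three seasons, with equal variance. Let r be the correlation of each later year with baseline, and s the correlation between Y1 and Y2. Then

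corr(Y1 − B, Y2 − B) = (1 + s − 2r) / (2(1 − r)).

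If s = r, this is 0.5, because the baseline is shared. If the two later seasons agree more closely with each other than with baseline, it is higher. For illustration, r = 0.5 and s = 0.8 give (1 + 0.8 − 1) / 1 = 0.8.

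**Error rates.** For bivariate normal statistics with correlation ρ:

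- either-year rule: 1 − P(|Z1| ≤ 1.96 and |Z2| ≤ 1.96);
- both-years rule: 2 × 0.05 minus the either-year figure.

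At ρ = 0 the either-year figure is 1 − 0.95² = 9.75%.

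| ρ | Either year | Either year, simulated t-tests, 23 v 23 | Both years |
|---|---|---|---|
| 0 | 9.75% | 9.8% | 0.25% |
| 0.5 | 9.1% | 9.0% | 0.9% |
| 0.7 | 8.4% | 8.3% | 1.7% |
| 0.8 | 7.8% | 7.7% | 2.2% |
| 0.9 | 7.0% | 6.9% | 3.0% |
| 0.99 | 5.7% | not run | 4.3% |

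The either-year figure falls to 5% only at ρ = 1.

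**Power under the both-years rule.** If each test alone has 80% power, the chance that both succeed is 0.80 × 0.80 = 64% at ρ = 0 and rises to 80% only at ρ = 1. The sample size makes no allowance for this loss.

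**The case against.** The strongest objection is that the protocol nowhere says that one significant year is enough. The primary outcome joins the two years with an *and*, which can be read as requiring both, and then 5% is respected. A reader might infer that the trial's 5% level is certainly breached. The text does not support that, because the excess depends on a success rule that is absent. This part of the objection stands.

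A reader might also count the interim as a third test. It is not one: if the look is the Year One t-test, that test is already counted, and without stopping rules the trial cannot end on it. Nor is it safe to say that the error nearly doubles. The factor is 1.8 at ρ = 0.5 but 1.4 at ρ = 0.9. Years One and Two are adjacent and share the same intervention, while baseline lies on the other side of the H1N1 season, so the higher correlations are plausible.

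It can further be said that the order of testing belongs in a statistical analysis plan, which is not at hand, and that the protocol itself calls this a feasibility study of new tools. These arguments lower the urgency but do not remove the point. Section 8.1 does more than leave a detail open: it sets 0.05 for each of two tests under the primary heading. The repeated-measures analysis does not rescue it, since it asks whether the effect changes over time and is not presented as one overall test replacing the two.

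**Conclusion.** The point holds in conditional form. The protocol tests its primary comparison in two years at 0.05 each and states no rule for combining them. If either year suffices, the two-sided false-positive rate is about 7% to 9% for correlations from 0.9 to 0.5, against a stated 5%. If both are required, 5% holds and power falls below the stated 80% unless the two tests are perfectly correlated. Discordant years have no stated meaning under the present text.

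The figures assume two-sided tests, no true effect in either year for the error rates, and a correlation that the documents do not give. They count only the two t-tests. The 90% benchmark, which section 8.1 also labels primary, is a possible further test and is not in the calculation. This should be corrected, but it is a matter of moderate weight.

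**What to change.** Before any Year One data are seen, name one primary comparison. One workable choice is the between-group difference in change from baseline to Year Two (2011-2012), at two-sided 0.05, with Year One tested for significance only if Year Two is significant. State that the Year One interim is descriptive and supports no efficacy claim. In the same edit, reconcile Study Outcomes with section 8.1 by making attainment of the 90% benchmark secondary. Otherwise a second outcome labelled primary remains, and the 5% is still not carried by one test.

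Other rules would also control the error if the investigators prefer to keep both years on an equal footing. Testing each year at 0.025 gives 4.7% overall at ρ = 0.5 and 3.6% at 0.9. Requiring both years also keeps within 5%, but the sample size should then be checked against that rule.

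The cost is a few sentences and no extra organizations or data. With Year Two as the deciding test, an effect seen only in Year One cannot be claimed as confirmatory. Organizations that leave after Year One would contribute to the primary test only through the multiple imputation planned in section 8.2.

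### For the change in immunization rate in a given year, section 8.1 plans an unadjusted t-test, a regression and multilevel models, says all analyses are adjusted, and does not say which one decides

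*Protocol*

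**What the plan says.** The opening of the Protocol's Statistical Methods section defines the primary analysis only as a comparison of the two groups, without naming a method. Section 8.1 then sets out, for the change in rate from the base year:

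- a test for each of Year One and Year Two: "we will use t-test to compare immunization rate difference means of the control group to the intervention group", followed at once by "We will consider *P* values < 0.05 to be significant";
- linear regression, with the same improvement from the base year as the response;
- an adjustment rule: "All analyses will be undertaken, adjusted for healthcare organization size", and also for baseline variables found to differ significantly between groups;
- "Multilevel models will be applied to take account of clustering at the healthcare organization level";
- a profile over baseline, Year One and Year Two, of which it says "This will be a repeated measures analysis", with the stated aim of seeing whether the effect differs between time points.

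The Primary Outcome text under Study Outcomes gives another method: "This will be assessed by conducting a time-series analysis on how each organization does against themselves and between the Intervention and Control Group". None of these is ranked, and none is called supportive.

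**The concern.** The t-test, the regression and the multilevel model all address the same question: did the change in rate in a given year differ between arms? They can give different P values. The t-test weights every organization equally and adjusts for nothing. The regression adjusts for size and for whatever baseline variables turn out significant. A multilevel model can weight organizations by precision, and the organizations are expected to be small, medium and large.

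The text also contradicts itself in two places. A two-sample t-test cannot be one of the analyses that are all adjusted. And the method given for assessing the primary outcome under Study Outcomes is not the one in section 8.1. Because the Protocol itself fixes these statements, a later analysis plan could settle them only by overriding one of them.

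At stake is a borderline result. With no deciding analysis named, the trial could be reported as positive or negative from its own planned tests, and nothing in the text prevents the choice being made after the results are known.

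**Working it through.** **The plan's own figure.** The Sample Size section states: "we will need a total of 46 clusters for 80% power and 5% significance". Its inputs are an intra-cluster correlation of 0.05, 150 personnel per cluster and a 20% difference. The control rate is not given. I assume 50% against 60%, which reads the 20% as relative.

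- Design effect: 1 + (150 − 1) × 0.05 = 8.45.
- Two-proportion formula, two-sided 5%, 80% power: 388 per arm, or 408 with continuity correction.
- Clusters: 2 × 388 × 8.45 / 150 = 43.7, so 44. With the correction, 2 × 408 × 8.45 / 150 = 45.97, so 46.

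The 46 therefore reproduces under that reading. If the 20% were absolute, only 10 to 14 clusters would be needed. What matters here is that the calculation allows for a single comparison at 5%, so it presupposes one deciding test.

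**False-positive rate for one year, no true effect.** Two simulations were run, both with 46 clusters, a 50% rate and an intra-cluster correlation of 0.05. Multilevel models were approximated by precision-weighted regressions at organization level.

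*Simulation A.* There were 5,000 trials per setting. Cluster sizes were assumed lognormal with mean 150 and coefficient of variation 1. The three analyses were the t-test, the size-adjusted regression and the precision-weighted model. Each alone gave about 5%. The chance that at least one gave P < 0.05 was:

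| Year-to-year cluster correlation (assumed) | At least one of three |
|---|---|
| 0.3 | 6.5% |
| 0.5 | 6.8% |
| 0.8 | 7.5% |

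*Simulation B.* There were 6,000 trials per setting. Cluster sizes were assumed to be 75, 150 or 300. The adjusted regression also took in the baseline rate and four unrelated baseline variables whenever these differed at P < 0.05, to mimic the adjustment rule. Each analysis alone gave 4.0-5.8%. The chance that at least one was significant was:

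| Correlation (assumed) | t-test or adjusted regression | plus weighted model of follow-up rate, baseline-adjusted | plus weighted model of follow-up rate, not baseline-adjusted |
|---|---|---|---|
| 0.3 | 5.9% | 8.7% | 9.8% |
| 0.5 | 6.6% | 8.6% | 10.6% |
| 0.7 | 6.0% | 7.8% | 10.4% |
| 0.9 | 6.9% | 8.0% | 10.9% |

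The last two columns give the 8-11% range. Most of the step up from 6-7% comes from modelling the follow-up rate instead of the change. Section 8.1 leaves that open, because it does not name the response of the multilevel models.

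Three independent tests would give 1 − 0.95³ = 14.3%. The tests share the same data and are strongly correlated, so the true figures lie well below that.

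**Disagreement.** With no effect, the t-test and the adjusted regression in simulation B differ on significance in 2.5-3% of trials. At an assumed 10-point effect, the one-year analyses of simulation A disagree in about 9-12% of trials.

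**Time series.** The Interventions section gives three annual values per organization: 2008-2009, 2010-2011 and 2011-2012. Only the first precedes the intervention, so no pre-intervention trend can be estimated for any organization.

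**The case against.** The best defence is that the t-test is the lead analysis. It comes first, the significance criterion follows it directly, and the opening of Statistical Methods prepares for it by reducing each organization to its mean. The multilevel models can be read as the way the regressions are fitted, not as another test. The time-series phrase can be read as loose wording for the before-after comparison, since talk of change scores follows it. On that reading there are about two routes, not five.

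Part of this stands. A reader might infer that five tests compete for one outcome in one year. The documents do not support that: the repeated-measures and time-series analyses span several years, and the stated aim of the repeated-measures analysis is a different question. A reader might also infer that P < 0.05 in any analysis counts as success, so that the error rate necessarily exceeds 5%. The text does not say so, and each analysis alone is valid at about 5%.

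The order of sentences is still only a hint. The statement that all analyses are adjusted comes later and undercuts it, and even two routes need a rule.

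Section 8.1 also calls attainment of the 90% benchmark the primary outcome. If that were fixed as primary, the t-test and linear regression on change would no longer compete for the main result. The point therefore applies to the continuous outcome only.

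**Conclusion.** The point holds for the continuous outcome in a given year. Section 8.1 contradicts itself on adjustment and names no deciding analysis, and the Study Outcomes text names a method that section 8.1 does not use.

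The size is moderate and conditional. If the deciding analysis is fixed in advance, the error rate is about 5%. If it is chosen after results are seen, or any significant one counts, the one-year rate is about 6.5-7.5%, and 8-11% with assumed covariate screening and a multilevel model of the follow-up rate. Disagreement at an assumed 10-point effect is roughly 10%. These figures rest on assumed cluster sizes, year-to-year correlations and baseline variables, on a 50% rate, and on two-sided testing, since the Protocol does not state sidedness. Larger figures result if a contrast pooling both years is counted, but that is not a one-year test.

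**What to change.** In section 8.1, name one deciding analysis of the change in rate at one time point, tested at two-sided 5%. A cluster-level or multilevel regression would serve. Adjust it for a fixed set: the two minimization variables (centre and organization size) and the baseline rate. Then:

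- remove from it the selection of covariates by baseline significance tests, since otherwise the deciding model still depends on the data;
- label the unadjusted t-test and the other models of the change as sensitivity analyses without significance claims, and limit the statement that all analyses are adjusted accordingly;
- keep the repeated-measures analysis for its stated aim, whether the effect differs between years;
- under Study Outcomes, replace the time-series wording with a reference to the deciding model.

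The cost is wording only, with no new data and no change to the 46 clusters. The downside is that the supportive analyses can no longer be cited as the trial's result.

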1.2 Poor Uptake of Influenza Vaccine by Healthcare Personnel

Despite abundant evidence of the safety and efficacy of the influenza vaccine, immunization rates among healthcare personnel in hospital and long-term settings remain well below the public health target of 90%. Current initiatives targeted at increasing healthcare personnel immunization rates are having limited success with healthcare personnel immunization rates as low as 2%, but averaging 40% - 60% in most healthcare facilities being reported (1,2,12).

1.3 Development of the Guide: “Successful Influenza Immunization Campaigns for Healthcare Personnel - A Guide for Campaign Planners”

Healthcare organizations have a wide variety of approaches to the immunization of their workers. Each influenza season, healthcare planners devote time and effort to encourage staff immunization through a seasonal influenza immunization campaign. While the majority of healthcare organizations are committed to vaccinating their personnel, they, however, work in isolation, with few resources and limited evidence to inform the development and running of a successful immunization campaign. Moreover, there are almost no additional resources available and often few opportunities to share ideas, ask questions, or boast successes with other organizations (14).

During the first year of the project team’s grant (2008-2009), we conducted a series of consultation meetings in Ontario and Nova Scotia with five long-term care homes and three acute care hospitals. We spoke to the influenza campaign teams typically comprising of occupational health and infection control leaders as well as other managers. The results of these consultation meetings led to the first draft of the Guide: “Successful Influenza Immunization Campaigns for Healthcare Personnel: A Guide for Campaign Planners” (see Appendix 1).

The goal of this study is to validate the Guide and additional web-based “grab and go” tools (the Toolkit).

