2.2 Rationale for a Cluster Randomized Control Trial

Our intention in choosing a cluster randomized control trial design is to evaluate the impact of a tool designed for use at an organizational level, rather than an individual level. In order to understand its impact we will assess changes within each organization according to the research objectives detailed herein.

1. Participants & Study Setting

At least 46 healthcare organizations from across Canada will be selected to participate in the study.

The Guide is designed to be used across different types of healthcare organizations. Potential healthcare organizations will be self-identified, recommended by a project team member, and/or selected from the Canadian Healthcare Association’s Guide to Healthcare Facilities. Selected sites must meet the following eligibility criteria:

- - Canadian healthcare organizations who conduct seasonal influenza immunization campaigns
  - Have a systematic approach to collecting healthcare personnel immunization rates and be able to provide accurate and timely reports of immunization rates for categories of healthcare personnel
  - Agree to be randomized to receive the Guide or receive no intervention
  - If randomized to receive the Guide, the organization, including the campaign team and senior management, agrees to commit to adhere to the steps in the Guide to plan, implement, monitor and evaluate their campaign

Influenza immunization campaigns in healthcare organizations in Canada normally begin in October and end in December, with ongoing influenza immunization continuing outside of the reporting parameters until April.

1. **Interventions**

All organizations who agree to participate in the study will agree to provide their immunization rates for three years:

2008-2009 – Baseline Year

2010-2011 – Year One

2011-2012 – Year Two

We did not choose 2009-2010 as the baseline year because of the impact of pandemic H1N1.

- 1. Intervention Group

For the intervention group, there will be a Guide facilitator provided by the project team, normally the Project Manager or their delegate. The role of the Guide facilitator will be to provide basic information about the Guide and to facilitate the use of the web-based tools.

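### The change-score t-test does not adjust for the 2008-2009 rate, so the stated 80% is not its power; always including that rate as a covariate costs almost nothing

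*Protocol*

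**What the plan says.** - Protocol 8.1 (Primary Outcome) forms the difference between each intervention year and baseline, and then "we will use t-test to compare immunization rate difference means of the control group to the intervention group", at the 5% level.
- The same section adds: "Linear regression models will be used for continuous outcome variables (improvement in healthcare personnel immunization rates from the base year"). These models adjust for organization size and for whichever baseline variables turn out significantly different between arms. Baseline rates are otherwise named only in interaction terms, to look for differential effects.
- It also plans multilevel, repeated-measures models, without saying how the baseline rate enters them.
- Under Interventions, the baseline year is 2008-2009 and the outcome years are 2010-2011 and 2011-2012: "We did not choose 2009-2010 as the baseline year because of the impact of pandemic H1N1". Every organization supplies its baseline rate.
- Under Sample Size, a formula for individually randomized trials is multiplied by a design effect, with the "intra-cluster correlation coefficient set at 0.05", an average of 150 personnel per organization and 23 organizations in the intervention arm. The conclusion is "we will need a total of 46 clusters for 80% power and 5% significance". On the effect: "The level of difference between intervention organizations and the control organizations set in determining the sample size was 20" per cent, without saying whether that is absolute or relative.

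**The concern.** Subtracting the baseline is not the same as conditioning on it. A change score carries the noise of both years. If the two years are only weakly correlated, the subtraction adds more noise than it removes, and the test does worse than one that ignores the baseline. Here the baseline lies two seasons before Year One and three before Year Two, with the pandemic season in between, so a weak correlation is possible. The sample size was worked out for rates at one time point and does not allow for this. With only 46 organizations, avoidable loss of precision matters, and the covariate that would prevent it is already being collected.

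**Working it through.** **Inputs.** From Sample Size: 23 organizations per arm, intra-cluster correlation 0.05, 150 per cluster, 80% power, 5% significance (two-sided is my assumption). From section 1.2: usual rates "averaging 40% - 60% in most healthcare facilities being reported"; I take 50% in the control arm. From Study Outcomes: the target is "a 10% improvement in healthcare personnel immunization rates from the base year (2008-2009"). The correlation r is not given anywhere, so I show a range. I assume equal variance in the baseline and follow-up years.

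**1. Reproduce the 46 clusters.** Design effect = 1 + 149 × 0.05 = 8.45. Reading 20% as relative, 50% becomes 60%, a 10-point difference with mean rate 0.55.
- Without continuity correction: n per arm = (1.96 + 0.84)² × 2 × 0.55 × 0.45 / 0.10² ≈ 389. Clusters = 2 × 389 × 8.45 / 150 = 43.8, so 44.
- With continuity correction: 408 per arm. 2 × 408 × 8.45 = 6895 personnel, and 6895 / 150 = 45.97, so 46.
- A comparison of 40% with 50% gives the same figures.
- A 20-point absolute difference (40% v 60%, or 50% v 70%) needs only 11 to 13 clusters.

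So 46 fits a difference of about 10 points. No step uses r.

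**2. What the stated 80% describes.** Variance of one organization's rate: v = 0.55 × 0.45 × 8.45 / 150 = 0.01394 (SD 0.118). Comparing follow-up rates alone, the standard error is √(2 × 0.01394 / 23) = 0.0348. The ratio 0.10 / 0.0348 = 2.87 gives 80% power (noncentral t, 44 df). The plan's 80% therefore belongs to a follow-up-only comparison.

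**3. The two ways of using the baseline.**
- Change score: variance 2(1 − r)v, 44 df.
- Baseline-adjusted: variance (1 − r²)v, times 1 + 1/42 = 1.024 for the expected chance imbalance in baseline, 43 df.

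At r = 0.3:
- Change score: 1.4 × 0.01394 = 0.0195; standard error 0.0412; ratio 2.43; power 66%.
- Adjusted: 0.91 × 1.024 × 0.01394 = 0.0130; standard error 0.0336; ratio 2.98; power 83%.

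| r | Change score | Baseline-adjusted |
|---|---|---|
| 0 | 51% | 79% |
| 0.3 | 66% | 83% |
| 0.5 | 80% | 89% |
| 0.7 | 95% | 97% |
| 0.8 | 99% | 99.6% |

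Simulation of 20,000 trials per value agreed: 66% v 83% at r = 0.3, 81% v 89% at 0.5 and 95% v 97% at 0.7. Taking the mean rate as exactly 0.50 (SD 0.119) moves these figures by about half a point at most.

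**4. Break-even.** 2(1 − r) = 1 at r = 0.5. Below that, the change score is noisier than ignoring baseline, and its power is under 80%.

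**5. Does the significance-triggered rule help?** Simulated at r = 0.4, adjusting only after a significant imbalance gave 73% to 74%. The change score alone gave about 73%, and always adjusting gave 85% to 86%. The rule recovers almost nothing.

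**6. If 20 percentage points was meant.** At r = 0 the change-score standard error is 0.0492. The ratio 0.20 / 0.0492 = 4.06 gives 98% power.

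**7. How low r would have to be.** The reliability of one organization's yearly rate is 0.05 / (0.05 + 0.95/150) = 0.89. With independent sampling errors between years, r below 0.5 needs a correlation between true rates below 0.5 / 0.89 = 0.56.

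**The case against.** The strongest reply is that the shortfall depends on a correlation the protocol does not give. A true-rate correlation under 0.56 is possible across the pandemic season but is not shown. Clusters larger than 150, or staff who stay on between seasons, would push r up. At r = 0.7 the gain from adjustment is about 2 points, and at 0.8 less than 1. This stands: a reader might infer that the trial is underpowered or will miss 80%, and the protocol does not support that.

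A second reply is that 20% may mean percentage points, in which case power is ample. That reading does not reproduce 46 clusters, but the protocol does not rule it out.

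A third concerns validity. A reader might infer that regression to the mean biases the result. It does not: under randomization the change-score test is unbiased and holds its size. Chance baseline imbalance is already counted in its variance and is not a further defect.

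A fourth is that modelling improvement from the base year might itself look like an error. It is not. With baseline as a covariate, regressing the change on arm gives exactly the same arm effect as regressing the follow-up rate.

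Finally, which test is primary is not settled. Section 8.1 also calls attainment of the 90% benchmark the primary outcome, and says that all analyses are adjusted for size, so calling the t-test strictly unadjusted is open to dispute. The repeated-measures model might bring the baseline in, but the text does not say how. None of this puts the baseline rate into any stated analysis unconditionally.

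**Conclusion.** The point holds as one of efficiency, not validity. The first test under Primary Outcome does not condition on the baseline rate, no stated analysis always does, and the stated 80% is not that test's power. The cost depends on r. For a 10-point difference, the change score gives up about 17 points of power against adjustment at r = 0.3, about 9 at r = 0.5, about 2 at r = 0.7 and almost nothing at 0.8. It drops below 80% only when r is under about 0.5. These figures assume a 50% control rate, equal variances in both years and the protocol's own intra-cluster correlation, cluster size and arm size. Adjustment was at least as powerful at every r examined, so the change is worth making without knowing r. It should be made, but the trial's validity does not hang on it.

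**What to change.** In section 8.1, for the continuous outcome, make the main comparison an organization-level linear regression of the follow-up rate (or, equivalently, the change) on arm. Always include the 2008-2009 rate and the two variables named for minimization (organization size and trial centre), whatever imbalance is observed. Delete the rule that admits baseline covariates after a significance test. Keep the t-test on change as a sensitivity analysis. State in Sample Size whether 20% is absolute or relative, and which correlation is assumed.

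The cost is a sentence or two of text and a few degrees of freedom: one for the baseline rate, worth about 1 point of power if r were 0 (80% to 79%), one for the two-level centre and two for the three-level size. No new data are needed. The competing statement that attainment of 90% is the primary outcome must be reconciled separately.
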